### Sample size

Sample size was calculated, considering a power of 80%, a significance level of 5% and a Cohen’s effect size of 0.8, adding 10% for possible losses and refusals, totaling 58 participants, divided equally into IG and CG.

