### Data collection

Data collection will be performed at baseline and three months later. A structured questionnaire was developed with sociodemographic and clinical information from family caregivers and older adults. All information regarding older adults will be provided by caregivers. Instruments that assess caregivers’ ability to care, ECCIID-AVC, their knowledge and performance in caring for older adults (Nursing Outcomes Classification (NOC)) as well as instruments that assess the burden of these caregivers (Caregiver Bunder Scale (CBS)) and the measure of functional independence of older adults (Functional Independence Measure (FIM)) will also be applied.

Regarding the instruments used in the study, the ECCIID-AVC assesses the different capabilities that family caregivers have or need to improve when providing care to dependent older adults after a stroke. In the reproducibility study of the Brazilian version, the ECCIID-AVC showed satisfactory test-retest reliability (Intraclass Correlation Coefficient = 0.94; 95% Confidence Interval = 0.91-0.96) and excellent internal consistency reliability (Cronbach’s alpha = 0.914)^(7)^.

The NOC is a standardized taxonomy for nursing-sensitive outcomes intended for clinical practice and with the objective of verifying changes in the condition of a patient, family or community after an applied nursing intervention^(8)^. For the present study, the outcomes “Knowledge: Stroke Management” and “Caregiver Performance: Direct Care” were selected. A group of ten experts with knowledge and experience in using this classification assisted the researchers in selecting the indicators for these two outcomes. For each selected indicator, a conceptual definition and an operational definition were constructed.

Family caregivers’ burden will be assessed using the CBS. This scale was adapted and validated for the Brazilian context by Medeiros *et al*.^(9)^ with a population of caregivers of patients with rheumatic diseases. The intraand inter-observer reproducibility coefficients were 0.87 and 0.92, respectively, and the Portuguese version proved to be a valid instrument^(9)^.

Older adults’ functional capacity will be assessed using the FIM. The scale was translated into Brazilian Portuguese in 2000 and underwent validity for the Brazilian context in 2004. The Brazilian version of the scale has good cultural equivalence and good reproducibility^(10)^.

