### Statistical methods

For data analysis, the intention-to-treat technique will be used. The difference between baseline and final scores will be assessed by paired Student’s t-test, with a 95% Confidence Interval. A p<0.05 value will be considered significant. For simultaneous intraand intergroup comparisons, the Generalized Estimating Equations model with Bonferroni adjustment will be used.

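### The planned GEE names no baseline covariate; adjusting the three-month comparison for the baseline score would gain precision at no cost

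*Protocol article*

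**What the plan says.** The Statistical methods section of the protocol article names two analyses. A paired t-test addresses the change from baseline to the final score. For comparing within and between groups at the same time, "the Generalized Estimating Equations model with Bonferroni adjustment will be used". The terms of that model are not listed, and no baseline covariate is mentioned.

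The design gives one measurement before and one after: "Data collection will be performed at baseline and three months later". The Allocation section places randomisation after the instruments have been applied, so the baseline scores precede allocation and are valid covariates.

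The Sample size section rests on "a Cohen’s effect size of 0.8", "considering a power of 80%, a significance level of 5"%, and ends by "adding 10% for possible losses and refusals, totaling 58 participants", split equally between the arms. It does not say which outcome the effect size refers to, or whether it is scaled by the SD of the score or of the change.

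**The concern.** With two arms and two time points, a GEE with group, time and their interaction treats baseline as a repeated outcome. Its interaction term is the difference between arms in mean change. Subtracting the whole baseline score is the best use of it only when ρ is 1. When ρ is below 0.5, subtraction adds more noise than it removes, and the change contrast is less precise than ignoring baseline. The other contrast available from such a model, the arms at three months, gains nothing from baseline. ANCOVA weights the baseline score by its observed relation to the outcome, so apart from one degree of freedom it is at least as precise as either.

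At stake is precision in a trial of 58 caregivers. Baseline is taken in hospital and follow-up three months after discharge, so a moderate or low ρ is possible, and in that range the choice of contrast matters most.

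**Working it through.** **Inputs.** From Sample size: d = 0.8, 80% power, 5% significance, 10% for losses, 1:1 allocation. Assumed: a two-sided test (one-sided would need only 20 per arm by the normal approximation); equal variance at both times; ρ over a range, because no value is given.

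**Reproducing the 58.** A two-sample t-test (noncentral t) needs 26 per arm, with power 80.7%. That is 52 in total; 52/0.9 = 57.8 and 52 × 1.1 = 57.2, and both round up to 58. This is the plain two-group calculation, with no correlation term.

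**Variances.** Let σ² be the raw-score variance. Per arm and per person:

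- three-month score alone: σ²
- change score: 2(1−ρ)σ²
- ANCOVA residual: (1−ρ²)σ²

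ANCOVA relative to change: (1−ρ²)/[2(1−ρ)] = (1+ρ)/2. This is below 1 for any ρ below 1. ANCOVA relative to the three-month score alone is 1−ρ². The change score matches the three-month score alone when 2(1−ρ) = 1, that is, at ρ = 0.5.

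In GEE models fitted to simulated data with group, time and group-by-time terms, the interaction estimate equalled the difference in mean change.

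**Power if d = 0.8 is on the raw-score SD, 26 per arm.** Effective d is 0.8/√[2(1−ρ)] for change and 0.8/√(1−ρ²) for ANCOVA. At ρ = 0.3 these are 0.8/√1.4 = 0.676 and 0.8/√0.91 = 0.839.

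| ρ | Change or group-by-time | ANCOVA | Three-month score alone |
|---|---|---|---|
| 0.2 | 61% | 82% | 81% |
| 0.3 | 67% | 84% | 81% |
| 0.4 | 73% | 87% | 81% |
| 0.5 | 81% | 90% | 81% |
| 0.6 | 89% | 94% | 81% |
| 0.7 | 95% | 98% | 81% |

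Allowing for the degree of freedom spent on the covariate lowers the ANCOVA figures by at most about one point (at ρ = 0, 79.9% against 80.7% for the unadjusted comparison). Simulation with 20,000 runs at ρ = 0.3 gave 66.8% for change and 83.4% for ANCOVA.

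**Power if d = 0.8 is on the change-score SD, 26 per arm.** The change contrast has 80.7% at any ρ. ANCOVA has effective d = 0.8/√[(1+ρ)/2]. At ρ = 0.3 this is 0.8/√0.65 = 0.992, power about 94%; at 0.5 about 90%; at 0.7, 0.8/√0.85 = 0.868, about 87%; at 0.9 about 83%.

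**Variance estimator, if GEE is kept.** With two balanced arms and complete data, the uncorrected sandwich variance of the interaction divides by n where the t-test divides by n−1. A z-test then rejects when |t| exceeds 1.96 × √(25/26) = 1.922. On 50 degrees of freedom that has probability 6.0%, against the nominal 5%.

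**The case against.** The strongest reply is that this is a condensed article. Model terms, covariates and the variance estimator are commonly left to the full protocol or analysis plan, and nothing in the text rules out baseline adjustment. That stands: the absence of a covariate from the article is not an error. What remains is that the article does commit to a method, and its natural form uses baseline less efficiently than a simple alternative.

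A reader might infer that the stated 80% power will not be delivered. The documents do not support this. A shortfall needs three things together: group-by-time as the deciding contrast, d on the raw-score SD, and ρ below 0.5. None is stated. A plain comparison at three months has the planned 81% on the raw-score reading; d on the change-score SD gives the change contrast 81%; and ρ above 0.5 puts it above plan. The only related figure is the ECCIID-AVC test-retest coefficient of 0.94. It measures reliability, not the correlation across discharge and three months of caregiving, and no such coefficient is given for the two NOC outcomes, which the Abstract also lists as primary. It does not settle ρ, but it gives no support for a low value.

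A reader might also infer that chance baseline imbalance passes whole into the result. It does not. Under the linear model used here an imbalance carries over multiplied by ρ, so it is small where ρ is low. Under randomisation it is already part of the unadjusted standard error and is not a bias.

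Nor is baseline discarded by a group-by-time GEE, since it enters as a repeated outcome. The uncorrected sandwich test is likewise not something the plan states. The 6% figure applies only if that estimator is used.

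**Conclusion.** The point holds as a free improvement in precision, not as a demonstrated loss of power. Whichever SD defines d, ANCOVA is at least as efficient as the change contrast, apart from the one degree of freedom. At ρ = 0.3 its variance is 0.65 times that of the change contrast; at ρ = 0.7 it is 0.85 times.

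In power, with 26 per arm, the gain at ρ = 0.3 is from about 67% to 84% on the raw-score basis, or from about 81% to 94% on the change-score basis. At ρ = 0.7 it is from about 95% to 98%, or from about 81% to 87%. The gain shrinks as ρ approaches 1.

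These figures assume that group-by-time is the intended contrast, equal variances at the two times, a linear relation to baseline, and 52 evaluable caregivers. They are for a single test at the 5% level, before any Bonferroni adjustment.

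**What to change.** In Statistical methods, name the primary between-group estimate: for each primary and secondary outcome, the three-month score compared between arms and adjusted for the same instrument's baseline score, by ANCOVA with t-based inference. A longitudinal model constrained to a common baseline mean in the two arms is an acceptable alternative, and it can keep all randomised caregivers.

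If GEE is retained, include that baseline adjustment or constraint and state a small-sample-corrected variance, such as Mancl-DeRouen.

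In Sample size, state which outcome and which SD the effect size of 0.8 refers to.

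The cost is a few sentences. Every baseline score is already collected before randomisation, and no additional participants or assessments are needed.

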### Data monitoring

All researchers involved in the study were properly trained and tested to assess agreement in the application of the instruments performed.

### Damages

The investigation process may cause fatigue and some discomfort to participants, in addition to possibly increasing mobile internet data consumption.

### Ethical approval in research

The project was approved by the Research Ethics Committee, under *Certificado de Apresentação para Apreciação Ética* (CAAE, Certificate of Presentation for Ethical Consideration), and its protocol is registered at clinicaltrial.gov.

### Consent

An Informed Consent Form (ICF) will be applied to family caregivers, and the voluntary nature of participation as well as anonymity will be ensured.

### Confidentiality

To access the information in medical records, legal requirements must be met and a term of commitment for use must be signed.

### Data access

Study data will be available for access.

### Disclosure policy

The results will be disclosed to the services in which the research will be carried out, to participants and to the scientific community.

## RESULTS

This research aims to provide support that demonstrates the effectiveness of virtual interventions as a means of education and development of care skills aimed at family caregivers of older adults who have suffered a stroke. This is a pioneering study in the country that values nurses’ educational role.

## DISCUSSION

Stroke is more common in older adults, and its consequences include motor, sensory and cognitive function disorders that reduce the ability to perform ADLs. After discharge, stroke survivors usually return home, where they can count on the support of caregivers.

Nurses play a fundamental role in educating stroke survivors and their family caregivers during hospitalization and in preparing for discharge, through guidance on the pathology, emotional support for caregivers and older adults, use of services available in the health network, performance of care activities and reduction of caregiver burden. Educational materials can facilitate this process^(6)^, and the educational manual used as the basis for the intervention proposed in this study is the first developed in the Brazilian context for family caregivers of older adults after stroke.

Interventions using digital technology have been described in the literature since 2010 through the use of telephones, video calls and, more recently, other technologies such as apps. The restrictions imposed by the pandemic have made the use of these resources indispensable, representing new forms of continuity of care. In developing countries, such as Brazil, these interventions still need to be further tested. In this scenario, MOOCs represent a positive educational alternative that deserves to be further explored in the health area^(5)^.

The use of PT is still in its infancy in nursing research, and this method is considered robust and adequate to assess the effect of the proposed intervention. The ECCIID-AVC, recently adapted and validated for use in Brazil, will be used for the first time in this study, assessing family caregivers’ ability to care. The choice of NOC to assess the outcomes of caregiver knowledge and performance also stands out as an innovation in this research, since there are currently no similar studies. The digital educational intervention, developed by nurses especially for this study, will be made available at the end of the research as a complementary tool for the education of patients and caregivers.

### Study limitations

Limitations of this study may include the fact that participants were recruited from a referral institution for stroke care that offers specialized care through a multidisciplinary team. Other possible limitations may include loss to follow-up due to death of stroke survivors, admission to long-term care facilities, or change of caregivers.

### Contributions to health, nursing or public policy

This research presents advances in nursing knowledge by promoting educational alternatives aimed at family caregivers of older adults who have suffered a stroke in the Brazilian context, constituting a technology for nursing assistance in transition of care.

## CONCLUSIONS

This study presented the protocol of a randomized PT aimed at family caregivers of older adult stroke survivors that aims to explore alternatives for transition of care from hospital to home with the support of digital technology.
